## Abstract

**Introduction:**

The increasing prevalence of type 2 diabetes mellitus (T2DM) presents a significant burden on affected individuals and healthcare systems internationally. There is, however, no agreed validated measure to infer diabetes severity from electronic health records (EHRs). We aim to quantify T2DM severity and validate it using clinical adverse outcomes.

**Methods and analysis:**

Primary care data from the Clinical Practice Research Datalink, linked hospitalisation and mortality records between April 2007 and March 2017 for patients with T2DM in England will be used to develop a clinical algorithm to grade T2DM severity. The EHR-based algorithm will incorporate main risk factors (severity domains) for adverse outcomes to stratify T2DM cohorts by baseline and longitudinal severity scores. Provisionally, T2DM severity domains, identified through a systematic review and expert opinion, are: diabetes duration, glycated haemoglobin, microvascular complications, comorbidities and coprescribed treatments. Severity scores will be developed by two approaches: (1) calculating a count score of severity domains; (2) through hierarchical stratification of complications. Regression models estimates will be used to calculate domains weights. Survival analyses for the association between weighted severity scores and future outcomes—cardiovascular events, hospitalisation (diabetes-related, cardiovascular) and mortality (diabetes-related, cardiovascular, all-cause mortality)—will be performed as statistical validation. The proposed EHR-based approach will quantify the T2DM severity for primary care performance management and inform the methodology for measuring severity of other primary care-managed chronic conditions. We anticipate that the developed algorithm will be a practical tool for practitioners, aid clinical management decision-making, inform stratified medicine, support future clinical trials and contribute to more effective service planning and policy-making.

**Ethics and dissemination:**

The study protocol was approved by the Independent Scientific Advisory Committee. Some data were presented at the National Institute for Health Research School for Primary Care Research Showcase, September 2017, Oxford, UK and the Diabetes UK Professional Conference March 2018, London, UK. The study findings will be disseminated in relevant academic conferences and peer-reviewed journals.

Strengths and limitations of this studyThis is the first UK-based study to develop a diabetes severity scoring tool based on real-world electronic healthcare data to grade people with type 2 diabetes by their clinical severity.The study will include a large sample size and use high-quality medical data routinely collected from general practices with access to linked national hospitalisation and cause-specific mortality data sets.The association between the computed severity scores and future adverse outcomes (cardiovascular event, hospitalisation and mortality) will be used to validate the developed severity algorithm.There is a possibility to miss other severity indicators not recorded in the data sources used such as pharmacy dispensing data.Given that the linkage scheme is only available for consented general practices in England, the study cohort will be restricted to eligible patients registered within England (form nearly 58% of total Clinical Practice Research Datalink general practices).

## Introduction

The worldwide prevalence of diabetes mellitus is increasing with WHO estimating that over 422 million adults had diabetes in 2016 with a growth in the global prevalence from 4.7% in 1980 to 8.5% in 2014.^1 2^ In the UK, the prevalence of type 2 diabetes mellitus (T2DM) has nearly doubled between 2004 and 2014.^3 4^ People with diabetes have a higher risk for morbidity and mortality when compared with individuals without diabetes,^3 5^ and hence the increasing prevalence presents a significant burden on healthcare resources. Diabetes management expenses are estimated to consume up to 11% of the total healthcare budget in the UK and USA.^6 7^ Diabetes is a complex metabolic condition, of an increasing severity,^8 9^ at individually varying levels, and progressive development of vascular complications and end organ damage over time. Diabetes is mainly managed in primary care in the UK,^10^ overall Europe,^11^ USA^12^ and Asia.^13 14^ In the UK, nearly 75% of the diabetes-associated costs relate to management of diabetes-related complications.^6^

The ‘severity’ of clinical conditions can be conceptualised as a progression of the underlying disease process. Increasing disease severity and development of associated complications lead to greater treatment complexity and clinical impact. The severity of chronic conditions, such as diabetes, has not been widely considered despite the clinical relevance and its likely impact on healthcare systems, where few studies have assessed disease severity among patients with T2DM or have quantified temporal trends or scores of severity.^15 16^

Severity scores could be clinically useful, particularly in T2DM; as such, a new summary score could contribute above what existing risk scores offer (eg, moving beyond risk for death) and also be highly relevant for use in six main clinical and research areas: (1) identifying complex patients with a higher need for future care; (2) identifying patients at early stages of disease (benchmarking); (3) providing information that will directly inform clinical care; (4) identifying trajectories in severity over time; (5) supporting research, for example, by serving as an important diabetes-specific covariate to consider in analyses, similarly to the Charlson Comorbidity Index, or as an outcome; and (6) providing data that will inform resource allocation in health systems, such as the National Health Service.

Here, we describe the conceptual development of a T2DM severity algorithm model, using electronic health records (EHRs) on clinical consultations and treatments. Our aim is to use routinely collected clinical and administrative data to develop a scoring tool which would quantify and grade the severity of T2DM. This model could potentially be used by clinicians to stratify patients based on disease severity and we aim to demonstrate potential advantages over similar risk scores. To validate the algorithm, our secondary aim is to examine the association of severity grades with risk of three main adverse outcomes: cardiovascular disease, hospitalisation and mortality. The developed severity stratification algorithm is anticipated to have direct impact on clinical practice and have wider implications on service planning and policy-making.

## Methods and analysis

### Data source

This study will use data from the Clinical Practice Research Datalink (CPRD). The CPRD is one of the world’s largest EHR with anonymised primary care records from over 650 general practices over the UK.^17^ Nearly 76% of all CPRD-registered patients are in England.^17^ CPRD data include clinical diagnoses, prescribed therapies, biochemical test results and referrals to healthcare services. The accuracy and completeness of diagnostic coding and validity of CPRD data, in clinical research, have been reported as excellent with positive predictive values (PPVs) of over 90% for nearly 14 conditions (including diabetes and cerebrovascular disease).^18^ PPVs were defined as the proportion of CPRD diagnoses that were validated as true cases when compared with a gold standard such as general practitioner (GP) questionnaire or primary care records.

Two metrics for research quality data, recommended to be used by researchers, are available for CPRD records.^17^ For patient-level data, the flag ‘acceptable’ indicates that a patient’s record has met certain quality standards such as registration status, valid age and gender and record of patient events. For practice-level data, the up-to-standard (UTS) date is used as a data quality measure. The UTS date is calculated for each CPRD general practice as the latest date at which the general practice meets minimum quality criteria based on two central concepts: the continuity of recorded data and the number of recorded deaths, in comparison to an expected national range.^17 19^

Nearly 75% of general practices in England (approximately 58% of all CPRD practices) have consented to the CPRD Linkage Scheme for access to a number of linked data sets and national disease registries.^17^ These include hospital data (including outpatient, admissions and accident and emergency (A&E) data), mortality records (held by the Office for National Statistics (ONS)), socioeconomic status and the cancer registry. The linked hospitalisation records, held by the Hospital Episode Statistics (HES), provide ethnicity data, admission and discharge dates, clinical diagnoses and procedures during hospitalisation recorded using the 10th revision of the International Classification of Diseases (ICD-10) and operating procedure codes. This study will only include patients registered with English general practices which provide UTS data and which participate in the CPRD Linkage Scheme.

### Study population

The study cohort will include individuals aged 35 years or over with T2DM (with ≥1 diagnostic code as in (online supplementary table S1) between 1 April 2007 and 31 March 2017. Patients with an ever record of type 1 diabetes (see online supplementary table S2) will be excluded unless they have records of non-insulin anti-diabetic therapies. We chose the study period after 2006 as the quality of CPRD data has improved substantially to adhere with the then introduced important changes to the national incentive scheme The Quality and Outcomes Framework (QOF), an incentivisation programme for all GP surgeries in the UK.^20 21^ QOF exception reporting process allows general practices to exclude patients from indicators or a clinical domain based on discretionary exception codes. However, evidence on the use of exception codes has shown that they are being used appropriately by practices and overall exception rates for diabetes patients are low.^22^

10.1136/bmjopen-2017-020926.supp1Supplementary data

For this cohort construction, we will consider implementing previously validated algorithms designed to identify diabetes cases by avoiding potential misclassification in routinely collected data such as CPRD.^23 24^ Eligible patients will be followed up until censored at the earliest instance of any of the following event dates: patient transferred out of the practice (any cause), last collection date for the practice, the study end on 31 March 2017 or death. The main demographic and clinical characteristics of the defined diabetes cohorts (such as age, gender, geographic region within England, patient-level and general practice-level social deprivation, body mass index (BMI) and baseline glycated haemoglobin (HbA_1c_)) will be identified. Based on our previous studies, the expected sample size in a year will include 11 000 patients with T2DM registered with English general practices linked to the HES Admitted Patient Care data set, HES Outpatient and HES A&E data sets. A random 80% of the identified diabetes cohort (training dataset) will be used to develop the severity tool, with the remaining 20% of the cohort used as a validation data set, as described below.

### Severity domains

A systematic literature search for studies that developed algorithms or models to assess and quantify the severity of diabetes was conducted to identify the domains and subdomains for T2DM severity (to be published separately). Also, expert clinical opinion from members of the research team was used to supplement the search process and identify possible omissions. Clinical members in the team include pharmacists ([name], [name]), GPs (CS, CM, [name], [name] and NQ), a consultant diabetologist ([name]) and a consultant cardiologist (MM), who used their expertise to create a list of relevant clinical domains for T2DM severity. The final domains to be included in the severity model will be decided during the analysis stage. Currently, the identified clinical domains that are relevant to the degree of progression of T2DM include: patient factors (diabetes duration (the period between T2DM diagnosis and the severity score estimation) and BMI), monitoring laboratory tests (HbA_1c_ categories (threshold of 7% [53 mmol/mol]), and blood glucose levels), type of anti-diabetic therapy, other prescribed medications (such as lipid-regulating medications and ACE inhibitors (ACEIs)), comorbidities (including diabetes-related complications, depression), hospitalisation and surgical interventions. Comorbidities will be identified using appropriate code lists and contribute to the severity score according to each score computing method. The identified domains and subdomains are described in table 1. Domains will also be reviewed by a panel of ‘experts by experience’ (people with lived experience of T2DM) to provide patient validation of the severity scoring tool.

**Table 1 T1:** The main (sub)domains identified to quantify the severity of type 2 diabetes

	Severity domain	Severity subdomain
1.	Risk factors*	Duration of type 2 diabetes^40^ Body mass index (BMI) Hypertension Hyperlipidaemia Personal/Family history of cardiovascular disease Blood glucose levels Glycated haemoglobin (HbA_1c_)^35^ Fasting blood glucose (FBG) and random blood glucose (RBG)
2.	Type/pattern of anti-diabetic treatment, insulin use and other therapies	Anti-diabetic therapy ever;^40^ Therapies with cardiovascular benefits versus other; Changes in drug treatments;^43^ or the number of prescribed treatments^42^ Insulin use: prescription ever or within 1 year of diagnosis; Insulin initiation:^15^ time to initiation Other therapies: ACE inhibitors (ACEI) and lipid-regulating therapies
3.	Diabetes-related microvascular complications^15 34^	Neuropathy (foot ulcer, Charcot foot, gangrene, amputation) Nephropathy Retinopathy (laser therapy and blindness)
4.	Renal disease	Microalbuminuria and proteinuria Moderate-severe chronic kidney disease (CKD) stages 3 and 4^34^ End-stage renal disease (ESRD): kidney transplant and dialysis
5.	Cardiovascular and cerebrovascular disease	Atherosclerosis^15 34^ Myocardial infarction (MI)^15 34^ Angina^15 34^ Atrial/ventricular fibrillation (AF)/(VF)^34^ Heart valve disease Heart failure (HF)^34^ Peripheral vascular disease (PVD)^34^ Transient ischaemic attack (TIA) Ischaemic stroke, haemorrhagic stroke^15 34^
6.	Cardiovascular and cerebrovascular interventions	Coronary artery bypass graft (CABG) Coronary artery interventions (PCI/PTCA) Endovascular aneurysm repair (EVAR) PVD stenting and bypass procedures Heart valve interventions Use of defibrillator Carotid artery events, stenting and bypass interventions
7.	Other comorbidities	Anxiety Depression Dementia Cognitive impairment
8.	Hospital admissions	Any-cause hospital admissions Diabetes-attributable admission Cardiovascular disease-related admission
9.	Emergency diabetes-related events	Hypoglycaemia Hyperosmolar hyperglycaemic state (HHS)^34^ Diabetic ketoacidosis (DKA) or other coma^34^

*Other demographic data (such as age, gender and the level of deprivation) are important predictors for adverse outcomes and will be included in the later risk prediction analysis.

The clinical Read codes for the defined severity domains codes and the product codes for drug therapies will be identified using the (pcdsearch) Stata user command.^25^ The (pcdsearch) command is a search programme developed to extract code lists from typically very long lookup files associated with primary care databases using an input file containing a list of stubs for codes of interest to be searched for. For CPRD, the lookup files Medical data set is searched for all clinical Read codes and the Product lookup file, that includes unique product codes, is searched for all treatments. The corresponding ICD-10 codes will be used to identify clinical domains recorded in the hospitalisation data and ONS mortality records. The relevant CPRD operational identification entities for the laboratory tests will be identified. This is an ongoing process whereby the final lists of domains and codes will be reached by consensus among the clinical members of the team. All code lists will be available on the online clinical code repository (ClinicalCodes.org).^26^

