### Study outcomes

The adverse outcomes of interest will be the development of the first event among cardiovascular disease (myocardial infarction, stroke), future hospitalisation (any hospitalisation, diabetes-related and cardiovascular hospitalisation) and death (diabetes-related mortality, cardiovascular mortality and all-cause mortality). Secondary outcome will be future hospitalisation due to hypoglycaemia, a relevant and potentially preventable adverse outcome. The hospitalisation and death outcomes will be identified using the linked HES and ONS mortality data, respectively. Similarly with severity domains, Read codes and ICD-10 codes (available on the ClinicalCodes.org online repository) will be used to identify the outcomes as appropriate.

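### Admissions, MI, stroke and hypoglycaemia are both score inputs and validation outcome types, and added value is tested only against demographics, so validation on these outcomes may credit event recurrence to T2DM severity

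*Protocol article*

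**What the plan says.** **Inputs.** Table 1 (Severity domains) lists the following among its subdomains:
- domain 5: "Myocardial infarction (MI" and "Ischaemic stroke, haemorrhagic stroke"
- domain 8: "Any-cause hospital admissions Diabetes-attributable admission Cardiovascular disease-related admission"
- domain 9, which begins: "Hypoglycaemia Hyperosmolar hyperglycaemic state (HHS"

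**Outcomes.** Study outcomes names the "development of the first event among cardiovascular disease (myocardial infarction, stroke", then "future hospitalisation (any hospitalisation, diabetes-related and cardiovascular hospitalisation", then three mortality outcomes. Hospitalisation for hypoglycaemia is the secondary outcome. The section on Severity algorithm validation repeats these in shorter form and does not say there that the cardiovascular event must be a first one.

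**Weights.** Under Diabetes severity algorithm, subdomain weights come from regressions with death as the primary and future hospitalisation as the secondary dependent variable.

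**Validation.** Performance is assessed in a random 20% of the cohort. Added value is tested by comparing the full model with one that holds age, gender and deprivation only.

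**Timing and scope.** Inputs come from a provisional look-back of 3 to 5 years, and validation is against future outcomes. The domain list is to be settled at the analysis stage. The section on longitudinal trends says that some domains may be dropped because of feedback, but it names only treatments and procedures that improve prognosis.

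**The concern.** The study aims to grade the severity of T2DM, and association with later outcomes is the evidence offered that the score does so. The limitations section says that questionnaire validation and replication in a separate data set are not possible, so this is the only quantitative validation planned.

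If a past event of a given type is in the score and a later event of that type is the outcome, part of any good result reflects recurrence. For MI, stroke, hypoglycaemia and diabetes-attributable admission, recurrence may well carry diabetes content. For any-cause admission it need not: a patient admitted repeatedly for unrelated illness scores higher and is then admitted again.

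The plan has no step that separates the two. Weights derived from future hospitalisation may favour prior admission. The demographics-only comparator assigns the whole gain to the severity domains. The 20% hold-out uses the same definitions as the 80%. The article foresees uses in triage and practice remuneration, where mistaking frequent admission for diabetes severity would matter.

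**Working it through.** **Step 1: match inputs to outcomes.**

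| Event type | Input (Table 1) | Validation outcome | Also used for weights |
|---|---|---|---|
| Any-cause admission | domain 8 | any hospitalisation | yes (future hospitalisation) |
| Diabetes admission | domain 8 | diabetes-related hospitalisation | as above |
| Cardiovascular admission | domain 8 | cardiovascular hospitalisation | as above |
| MI, stroke | domain 5 | cardiovascular event | no |
| Hypoglycaemia | domain 9 | hypoglycaemia admission (secondary) | no |
| Death (three types) | none | mortality | yes (primary) |

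The three admission inputs match the three hospitalisation outcomes one for one. Death is not an input.

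**Step 2: size.** The article gives no event rates or performance figures, so there is nothing to reproduce and every parameter below is an assumption. Age, true diabetes severity S and non-diabetes frailty F are independent standard normal variables. A diabetes-specific score is S plus noise (SD 0.7). The admission risk is

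logit P = −1.4 + 0.4·age + bS·S + bF·F,

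which gives an event risk of 20–25%. Prior and later admission are drawn separately from this same risk, so no event stands on both sides. There is one data set of N = 200,000 per scenario; logistic models are fitted in 80% and the AUC is taken in the other 20%.

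Models: A = age; B = age + diabetes score; C = age + prior admission; Full = age + diabetes score + prior admission.

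| bS | bF | A | B | C | Full | Full−A | Full−B | Full−C |
|---|---|---|---|---|---|---|---|---|
| 0 | 0 | 0.607 | 0.607 | 0.607 | 0.607 | 0.000 | 0.000 | 0.000 |
| 0 | 0.5 | 0.605 | 0.605 | 0.610 | 0.610 | 0.005 | 0.005 | 0.000 |
| 0 | 1.0 | 0.594 | 0.594 | 0.629 | 0.629 | 0.035 | 0.035 | 0.000 |
| 0.3 | 0 | 0.609 | 0.633 | 0.610 | 0.633 | 0.024 | 0.000 | 0.023 |
| 0.3 | 0.5 | 0.603 | 0.624 | 0.610 | 0.628 | 0.025 | 0.004 | 0.018 |
| 0.3 | 1.0 | 0.592 | 0.609 | 0.631 | 0.639 | 0.047 | 0.030 | 0.008 |
| 0.5 | 0 | 0.603 | 0.650 | 0.607 | 0.650 | 0.047 | 0.000 | 0.043 |
| 0.5 | 0.5 | 0.603 | 0.648 | 0.616 | 0.652 | 0.049 | 0.004 | 0.036 |
| 0.5 | 1.0 | 0.589 | 0.626 | 0.638 | 0.658 | 0.069 | 0.032 | 0.020 |

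**Step 3: read the table.**
- Full−B is what prior admission adds: 0.000 with no frailty, 0.004–0.005 at bF = 0.5, and 0.030–0.035 at bF = 1.0.
- Full−A is the comparison the plan describes. It equals 0.047 both at (bS 0.3, bF 1.0), where prior admission supplies 0.030, and at (bS 0.5, bF 0), where it supplies 0.000. A demographics-only comparator cannot tell these cases apart.
- With no diabetes effect and strong frailty (row 3), the plan's comparison still shows a gain of 0.035. Against model C the gain is 0.000.
- Full−C is conservative, because prior admission carries some true severity. At (0.5, 0) it is 0.043, against 0.047 over age alone. Reporting both contrasts brackets the answer.

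**The case against.** A past event that predicts a later, different event is ordinary prognosis. A reader might infer that the validation is circular. The article does not support that: inputs come from a look-back window and outcomes are described as future. Circularity needs the same event on both sides. If 10% or 25% of outcome events were also counted as inputs, the simulated gain would be 0.010–0.065 or 0.047–0.103, but the article plans no such double counting. A missing index-date rule is detail that the full protocol or analysis plan may hold.

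A reader might also take *first event* to be incompatible with scoring prior MI or stroke, or conclude that the highest-scoring patients cannot have the outcome. Neither follows. First after the score date is a compatible reading. Under a first-ever reading, patients with prior events leave the risk set, so the overlapping input cannot inflate that result. The score also spans nine domains, so patients can score high without MI or stroke. The wording still needs settling, because the first reading mixes incident and recurrent events.

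Other points on that side:
- The lack of diabetes content applies fully to any-cause admissions only. This stands and limits the point.
- The domain list is provisional, and the abstract's short list does not name admissions. However, the main text and Table 1 do, and the only exclusion discussed does not cover them. The provisional status permits a remedy but does not plan one.
- Mortality validation is free of the overlap. This stands.
- One stated use is to identify patients with greater future care needs, for which prior admissions are legitimate predictors. This stands, and it is why the full score should be kept rather than replaced by reduced scores as the main result.

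**Conclusion.** The overlap of event types is in the text, and the planned comparison cannot separate diabetes severity from event recurrence. Results for hospitalisation, MI/stroke and hypoglycaemia admission *may* therefore overstate what diabetes severity contributes; the documents do not show that they *will*. The concern is greatest for any-cause admissions and does not extend to mortality.

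The size is not known. The range of 0.000–0.035 in AUC rests on the assumed logistic model, equal prior and later risk, strict time separation and frailty coefficients of 0 to 1. It was computed for admissions, not for MI/stroke or hypoglycaemia.

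Larger figures can be produced but measure something else. With assumed admission rates of 0.2–0.4 per year and frailty variance of 1–2, a single yes/no item for admission in the past 3 years gives an AUC of 0.63–0.72 for the next year. Prior MI or stroke alone (assumed prevalence 15–25%, hazard ratio 2–3, baseline 1.5% per year) gives 0.56–0.63 over 5 years. These are stand-alone values, and a reader should not take them as inflation of the full score's performance.

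**What to change.** Keep the full score as planned, and add the following to the validation:

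1. For each affected outcome, report performance with and without the overlapping input: at least without domain 8 for the hospitalisation outcomes, and without hypoglycaemia for hypoglycaemia admission.
2. Beside the demographics-only model, add a comparator of demographics plus prior events of the same type as the outcome.
3. State that the cardiovascular outcome is the first MI or stroke after the score date, use the same wording in Study outcomes and Severity algorithm validation, and report it separately for patients with and without prior MI or stroke.

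This costs a few extra validation runs on data already held, with no new data collection. The gain attributed to diabetes severity may come out lower, and the MI/stroke strata will be smaller than the whole validation set.

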### Statistical analyses

#### Diabetes severity algorithm

Using annual data bins and grouping diabetes patients in the training data set (include random 80% of the total diabetes cohort) from 1 April to 31 March between 2007 and 2017, the developed diabetes algorithm will grade the severity of T2DM using predefined (sub)domains. Our study period (after 2006) was selected to ensure very high data quality in primary care, while the addition of secondary care data will make our analyses even more robust, in terms of accurately classifying T2DM severity levels.

We will consider two approaches to derive numerical or categorical diabetes severity scores or levels. First, we will use a binary classification (severity indicator: present/absent) within each subdomain and calculate an aggregate score. The second approach, through hierarchical stratification of end organ microvascular and macrovascular complications, will involve increasing weighting within each subdomain, as severity increases where scores of 1, 2 or three on each subdomain will be assigned based on clinical input in terms of severity. Then, regression models, using death (primary outcome) and future hospitalisation (secondary outcome) as dependent variable, will be fitted from which the weights of its estimates will be used to calculate the weights for severity subdomains. The highest possible severity score will be known when the final list of included domains and subdomains is decided. Hierarchical diagrams of the clinical severity of identified diabetes-related complications domains (figure 1), cerebrovascular domains (figure 2) and cardiovascular (figures 3 and 4, online supplementary figures S1 and S2) domains are presented.

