#### Severity algorithm validation

When we have developed a first version of the severity score tool, it will be validated statistically by quantifying the association of severity scores to future adverse outcomes. The primary outcome will be developing a cardiovascular event (myocardial infarction, stroke), future hospitalisation and death (diabetes-related mortality, cardiovascular mortality and all-cause mortality). A secondary adverse outcome will be future hospital admission due to hypoglycaemia, a relevant and potentially preventable adverse outcome. Cox proportional hazards (after assessing proportional hazards assumption) and/or competing-risks regressions will be used to perform survival analyses and assess the relationship between the severity score and outcomes controlling for all available patient characteristics (such as age, gender, ethnicity and level of social deprivation). We aim to analyse and assess how severity scores differ across different levels of these variables. As stated earlier, a random 20% of the study cohort (validation data set) will be used to validate the performance of the severity algorithm that was developed in the training data set (80% of the diabetes cohort). Using the calculated subdomains weights (derived by the regression model estimates), Cox regression analysis will be used to validate the developed severity algorithm and we will assess the model performance using relevant measures (such as area under the receiver operating characteristic curve). Using this analysis, we will also test how much the ’sophisticated' full model that includes all relevant severity domains will add in terms of predictive validity of the adverse outcomes over a simpler model that includes demographic data (age, gender and level of social deprivation) alone.

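### As the steps are ordered, age, gender and deprivation enter only after the subdomain weights have been derived from death and hospitalisation, so the weights are open to confounding by age

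*Protocol article*

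**What the plan says.** All places are in the Protocol article.

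- **Severity domains, Table 1 footnote.** Age, gender and deprivation are not listed as severity domains. They "are important predictors for adverse outcomes and will be included in the later risk prediction analysis".
- **Diabetes severity algorithm.** In the training data, "regression models, using death (primary outcome) and future hospitalisation (secondary outcome) as dependent variable, will be fitted", and "the weights of its estimates will be used to calculate the weights for severity subdomains". No covariate list is given, and no demographic term is named.
- **Severity algorithm validation.** The score is related to outcomes "controlling for all available patient characteristics (such as age, gender, ethnicity and level of social deprivation". The order of steps is explicit: "Using the calculated subdomains weights (derived by the regression model estimates), Cox regression analysis will be used to validate the developed severity algorithm". The full model is then judged by what it adds "over a simpler model that includes demographic data (age, gender and level of social deprivation) alone".
- **Abstract.** The order is the same: regression estimates give the weights, and survival analyses of the weighted score follow.
- **Study population.** "The study cohort will include individuals aged 35 years or over with T2DM". No upper age limit is stated.

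**The concern.** The regression coefficients are the product here, because they become the weights. The plan itself calls age an important predictor of the outcomes. Table 1 contains many subdomains that plausibly become commoner with age, such as dementia, moderate to severe kidney disease, heart failure, atrial fibrillation, hypertension and diabetes duration. It may also contain some that are commoner in younger patients, such as raised HbA1c. If age is left out of the regression on death, each coefficient takes up part of the age effect, in a direction and amount set by that subdomain's relation to age.

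The score would then partly rank patients by age. Three uses in the document would suffer. The planned description of how scores differ across demographic groups would contain a difference built in by the weights. In the comparison with the demographics-only model, any age signal in the score would duplicate what the comparator already holds. The proposed uses for triage, remuneration and matching would rest on weights that do not measure diabetes severity alone.

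**Working it through.** **1. Is there a figure to reproduce?** No. The document gives no age effect, event rate, subdomain prevalence or age–subdomain association. Every numerical input below is an assumption.

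**2. Direction.** Let γ be the log hazard of death per decade of age, and δ_j the difference in age (in decades) associated with subdomain j, given the other subdomains in the model. To a first approximation, the coefficient without age is

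β_j(no age) ≈ β_j + γ·δ_j.

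The weight rises if δ_j > 0, falls if δ_j < 0, and hardly moves if δ_j is near 0. With more age-related subdomains in the model, these jointly stand in for part of age, so δ_j and the bias shrink.

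**3. Equal true effects.** Assumed: 40,000 patients; age mean 65, SD 12, limited to 35–95; 5 years of follow-up; hazard of 0.02 per year at age 65 with no subdomain present. Four binary subdomains each have a true HR of 1.5, prevalence at age 65 of 15%, 20%, 20% and 30%, and log odds per decade of age of +0.8, +0.4, 0 and −0.3. Cox model estimates without age:

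| Death HR per decade of age | Strongly age-positive | Moderately age-positive | Age-neutral | Age-negative |
|---|---|---|---|---|
| 1.0 | 1.52 | 1.50 | 1.48 | 1.55 |
| 1.5 | 2.19 | 1.81 | 1.46 | 1.30 |
| 2.0 | 2.68 | 1.95 | 1.51 | 1.18 |
| 2.5 | 2.88 | 2.03 | 1.43 | 1.07 |

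With age in the model, all estimates lie between 1.45 and 1.56.

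The weights are log hazard ratios. At 1.5 per decade, the first and last subdomains differ by ln 2.19 / ln 1.30 = 0.784 / 0.262 ≈ 3.0. At 2.0 per decade, they differ by ln 2.68 / ln 1.18 = 0.986 / 0.166 ≈ 6. The true ratio is 1. The distortion disappears only when age has no effect on death.

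**4. Named subdomains, small and large models.** Assumed: 200,000 patients; age mean 63, SD 13; uniform censoring up to 10 years; death HR per year of age 1.07 to 1.10 (1.07^10 = 1.97 and 1.10^10 = 2.59 per decade). Subdomain odds ratios per decade of age: dementia 3.5, kidney disease 2.5, hypertension 1.6, HbA1c above 7% 0.75. The larger model adds 30 subdomains with odds ratios of 1.2–2.2 per decade, prevalence 3–20% and true HR 1.2. Estimates without age:

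| Subdomain | True HR | Few subdomains | 30 more subdomains |
|---|---|---|---|
| Dementia | 2.0 | about 4–5 | about 2.7–3.1 |
| Kidney disease | 1.4 | 2.5–2.9 | 1.9 |
| Hypertension | 1.0 | 1.4–1.5 | 1.15–1.23 |
| HbA1c above 7% | 1.25 | 0.94–1.01 | 1.06–1.14 |

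As weights in the larger model: dementia gets ln 2.7 / ln 2.0 = 0.993 / 0.693 = 1.4 to ln 3.1 / ln 2.0 = 1.131 / 0.693 = 1.6 times its true weight. HbA1c gets ln 1.06 / ln 1.25 = 0.058 / 0.223 = 0.26 to ln 1.14 / ln 1.25 = 0.131 / 0.223 = 0.59 times its true weight.

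**5. Can validation repair this?** The score is S = Σ w_j x_j with w_j fixed. The validation model is log hazard = log baseline + θS + demographic terms. It estimates one θ, which multiplies every w_j alike, so each ratio w_j / w_k stays as it was set in the training data.

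**The case against.** The strongest objection is that the document never says age is left out of the weighting regression. The Diabetes severity algorithm section lists no covariates at all, included or excluded. The footnote explains why demographics are not domains, and its word for the subsequent analysis could mean any step after domain identification, the weighting regressions among them. The article may also condense a fuller protocol. This stands as a limit: exclusion of age is the most natural reading of three sections taken together, not a stated decision, and a reader who infers that the plan has ruled age out goes further than the text. It does not remove the point. The only adjustment written down comes after the weights are calculated, and following the plan in that order would confound them.

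A second objection concerns size. Table 1 has several dozen subdomains, and fitting them jointly reduces the bias. This also stands, and the second column of results in the last table reflects it. A reader might infer from the small model that the HbA1c weight vanishes or reverses. With 30 further age-related subdomains it stays positive, though much reduced. Recovery of the true values once age is added is also partly by construction, since age is the only omitted confounder simulated.

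A reader might further infer that a young patient with poor control would be graded as mild. That is not shown. HbA1c is one item among many, alongside insulin use, emergency diabetes events and microvascular complications. The scoring starts from a count or from clinically assigned levels of 1 to 3, and patients and carers will take part in an exercise on the weights.

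The planned comparison across demographic groups and the demographics-only comparator could expose a score that tracks age. They would not correct its weights.

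**Conclusion.** The point holds as a fault in the order of the steps as written. On the most natural reading, the weights are derived without demographic adjustment and are confounded by age, upward or downward according to each subdomain's relation to age. Adjustment at validation comes too late to change the relative weights.

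The size cannot be fixed from the document. Under the assumptions shown, dementia with a true HR of 2.0 is estimated at about 4 to 5 in a small model and about 2.7 to 3.1 in one nearer the planned breadth. HbA1c with a true HR of 1.25 falls to about 0.94 to 1.14 across both. The HbA1c result also assumes that raised values are commoner in younger patients. Only death was simulated. Future hospitalisation as a weighting outcome, and the effects of omitting gender and deprivation, were not quantified.

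**What to change.** In the Diabetes severity algorithm section, state that the weight-deriving regressions in the training set include age (flexibly, for example as a restricted cubic spline), gender and deprivation as adjustment terms alongside the subdomains, and that the score is built from the subdomain coefficients only. Amend the Table 1 footnote to say that demographics stay outside the score but are adjusted for when the weights are derived. If the full protocol already specifies this, the article need only say so.

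The cost is a sentence of model specification and a reworded footnote. The variables are already among the cohort characteristics to be extracted, and keeping demographics out of the score is preserved.
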